### Statistical analysis

3.5

Statistical analyses are prespecified using standard software (e.g., SPSS, R, or Stata). Two-sided tests are used with a significance level of α = 0.05.

#### Descriptive statistics

3.5.1

Statistical analyses are prespecified using standard software (e.g., SPSS, R, or Stata). Continuous variables are expressed as mean ± SD or median (IQR), depending on distribution. The clinic-based prevalence of PHQ-9 ≥ 10 is estimated with 95% confidence intervals. We also summarize selected workflow-related indicators, including completion rates of questionnaires and vascular measurements and the proportion of screen-positive participants who complete referral when indicated. These measures are summarized descriptively [proportions with 95% CIs; time burden as median (IQR)] without hypothesis testing.

#### Group comparisons

3.5.2

Participants will be grouped according to the primary outcome definition (PHQ-9 ≥ 10 vs. < 10). Between-group comparisons will evaluate differences in study indicators [gastric histopathology, vascular indices (e.g., RI, PI), baPWV, ABI/TBI, HRV, and scale scores] between PHQ-9 screening groups (≥0 vs. <10), while baseline demographics/clinical characteristics will be presented descriptively (Table 1). Comparisons of multimodal vascular, autonomic, and psychiatric measures between PHQ-9 screening groups (≥10 vs. <10) will be presented in Table 2.

**TABLE 1 T1:** Baseline characteristics of the study participants according to depressive symptom status.

Variable	Total (*n* = …)	PHQ-9 < 10 (*n* = …)	PHQ-9 ≥ 10 (*n* = …)	SMDs
Demographics				
Age, years				
Female, *n* (%)				
Body mass index, kg/m^2^				
Lifestyle and comorbidities				
Current smoker, *n* (%)				
Alcohol use, *n* (%)				
Hypertension, *n* (%)				
Diabetes mellitus, *n* (%)				
Dyslipidaemia, *n* (%)				
History of cardiovascular disease, *n* (%)				
Gastric/endoscopic–histological features				
OLGA stage 0–II, *n* (%)				
OLGA stage III–IV, *n* (%)				
OLGIM stage 0–II, *n* (%)				
OLGIM stage III–IV, *n* (%)				
*H. pylori* positive, *n* (%)				
Psychiatric and symptom scales				
GAD-7 total score				
PSQI total score				
GSRS total score (and subscales if used)				
HRQoL physical component score				
HRQoL mental component score				

**TABLE 2 T2:** Multimodal vascular, autonomic and psychiatric profiles according to depressive symptom status.

Variable	PHQ-9 < 10 (*n* = …)	PHQ-9 ≥ 10 (*n* = …)
Peripheral vascular ultrasound (dorsalis pedis artery)		
Inner diameter (mm)		
PSV (cm/s)		
EDV (cm/s)		
RI		
PI		
Triphasic waveform, *n* (%)		
Biphasic waveform, *n* (%)		
Monophasic waveform, *n* (%)		
Arterial stiffness and peripheral artery indices		
baPWV (cm/s)		
ABI		
TBI (if available)		
Autonomic and physiological measures		
Systolic blood pressure (mmHg)		
Diastolic blood pressure (mmHg)		
Resting heart rate (bpm)		
SDNN (ms)		
*RMSSD (ms)*		
Psychiatric and symptom measures		
GAD-7 total score		
PSQI total score		
GSRS total score (and subscales if used)		
HRQoL physical component score		
HRQoL mental component score		

Baseline characteristics are summarized descriptively and quantified using standardized mean differences (SMDs) rather than hypothesis testing; *p*-values will not be reported for Table 1. Formal statistical testing is used for prespecified exposure–outcome comparisons and model estimation as described below:

① *t*-test for normally distributed continuous variables with equal variances;

② Mann–Whitney U for non-normal or heteroscedastic variables;

③ χ^2^ test or Fisher’s exact test for categorical data.

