### Sample size and effect size estimation

3.6

The primary outcome is concurrent depressive symptom burden defined as PHQ-9 ≥ 10. The primary exposures of interest are dorsalis pedis artery Doppler indices, including resistive index and pulsatility index, together with arterial stiffness measures such as brachial–ankle pulse wave velocity.

Previous studies in populations with functional dyspepsia or chronic gastritis have reported a prevalence of PHQ-9 ≥ 10 in approximately 20%–30%. Although specific data in CAG are limited, we conservatively assume a similar prevalence, and the expected prevalence of moderate-to-severe depressive symptoms in our study sample is estimated at 25%.

To ensure model stability in multivariable logistic regression, we adopt the empirical rule of at least 10 events per variable (EPV ≥ 10). This sample size also permits estimating the prevalence of PHQ-9 ≥ 10 with acceptable precision (95% CI) in clinic-based CAG populations. Given that we plan to include approximately 10–12 covariates (including key vascular exposures and confounders), a minimum of 100–120 events (i.e., participants with PHQ-9 ≥ 10) is required. Assuming a 25% event rate, this translates to a total sample size of approximately 400–480 participants. Accounting for potential 10% missing data or incomplete assessments (e.g., partial vascular/HRV measurements), the target enrollment is set at 450–520 participants. Missingness will be summarized by variable and mechanism will be explored. Multiple imputation by chained equations (MICE) is used for covariates (and exposures if missingness is non-negligible), with the outcome included in the imputation model. Primary analyses report MI estimates; complete-case analyses are presented as sensitivity analyses.

If the observed prevalence of PHQ-9 ≥ 10 is substantially lower than anticipated and the number of events is insufficient for the prespecified multivariable model, we will reduce model complexity by prioritizing predefined core predictors and, if necessary, use penalized regression approaches to improve model stability.

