### Missing data handling and internal validation

3.7

Missingness is summarized by variable. The primary outcome is not imputed; however, the outcome is included as a predictor in the imputation models for covariates/exposures. Multiple imputation by chained equations (MICE) is used for covariates (and for exposures if missingness is non-negligible and plausibly missing at random), with the outcome included in the imputation model. Primary analyses report pooled estimates from imputed datasets, while complete-case analyses are presented as sensitivity analyses.

If missingness is high, we may simplify the model or transparently report limitations.

To assess model robustness and avoid overfitting in multimodal classification models for identifying PHQ-9 ≥ 10 at baseline, internal validation is performed using bootstrapping (e.g., 500–1,000 resamples) to obtain optimism-corrected performance metrics (AUC, calibration slope/intercept, Brier score). Corrected AUC values and 95% CIs are calculated, and model performance variability across samples is examined. These results help evaluate the generalizability of the model and will be discussed in the final manuscript. Sample size is driven by model stability and planned internal validation. Assuming ∼15%–25% prevalence of PHQ-9 ≥ 10, the expected number of events will support parsimonious models with prespecified key predictors, with shrinkage/internal validation to mitigate overfitting.

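### Section 3.5.2 uses the Mann–Whitney test as the remedy for unequal variances, but in groups this unequal it does not hold the 5% level; minor, as only the unadjusted comparisons are affected

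*Protocol article*

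**What the plan says.** Section 3.5.2 (Group comparisons) compares participants with PHQ-9 of 10 or more against those below 10 on histopathology, vascular indices, baPWV, ABI/TBI, HRV and scale scores. The t-test is reserved "for normally distributed continuous variables with equal variances". Everything else that is continuous falls under "Mann–Whitney U for non-normal or heteroscedastic variables". No test that allows unequal variances is named.

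The same section gives these comparisons inferential status: "Formal statistical testing is used for prespecified exposure–outcome comparisons and model estimation as described below". Section 3.5 adds: "Two-sided tests are used with a significance level of α = 0.05".

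Group sizes are set by prevalence, not by design. Section 3.6 assumes 25% screen-positive. Section 3.7 allows for less: "Assuming ∼15%–25% prevalence of PHQ-9 ≥ 10, the expected number of events will support parsimonious models with prespecified key predictors".

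**The concern.** The usual Mann–Whitney p-value uses a variance that is correct when the two distributions are identical. If the spreads differ, that variance is wrong even when the groups share the same mean and median and neither tends to give larger values. Unequal group sizes make this worse. The test then rejects too often if the smaller group is the more variable, and too seldom if it is the less variable.

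Non-normality is a conventional reason to consider a rank test. Unequal variance is not, yet the rule treats the two alike. In the normal but heteroscedastic case, it selects the test under the very condition in which the test loses its nominal level. At stake is whether the two-group p-values for such measures can be read as tests of location at 5%.

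**Working it through.** **Group sizes.** The article's own enrolment figure comes first, because it fixes the group sizes.

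- Lower end: 100 events / 0.25 = 400; 400 / 0.9 = 445 after rounding up, against the stated 450.
- Upper end: 120 / 0.25 = 480; 480 / 0.9 = 534, against the stated 520.

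Both are within 3%, so the stated totals are used.

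- At 25%: 112 vs 338 (N = 450) and 130 vs 390 (N = 520), about 1:3.
- At 15%: 68 vs 382 and 78 vs 442; 0.85 / 0.15 gives about 1:5.7.

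**Assumption.** The article states no SDs. The SD ratio (screen-positive over screen-negative) was therefore varied from 0.5 to 2.

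**Large-sample formula.** For normal data with equal means, group sizes n1 and n2 and SDs s1 and s2:

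- V_null = (1/12)(1/n1 + 1/n2), the variance the test assumes.
- V_true = arcsin(r1)/(2π n1) + arcsin(r2)/(2π n2), with r_i = s_i²/(s1² + s2²).
- True size = 2[1 − Φ(1.96 √(V_null/V_true))].

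Worked case, 112 vs 338, SD ratio 2, so r1 = 0.8 and r2 = 0.2:

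- V_null = 0.08333 × (0.008929 + 0.002959) = 0.000991.
- V_true = 0.14758/112 + 0.03205/338 = 0.001318 + 0.000095 = 0.001413.
- √(0.000991/0.001413) = 0.837; 1.96 × 0.837 = 1.641; size = 10.1%.

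With SD ratio 0.5, r1 and r2 swap: V_true = 0.000286 + 0.000437 = 0.000723, the multiplier is 1.171, and the size is 2.2%. With equal SDs each arcsine term is 1/12, V_true equals V_null, and the size is 5%.

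**Simulation.** 20,000 data sets per scenario, normal data, equal means, two-sided 5%. Percentage rejecting:

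| Groups | SD ratio | Mann–Whitney | Formula | Welch | Pooled t |
|---|---|---|---|---|---|
| 112 vs 338 | 1 | 5.0 | 5.0 | 5.0 | 5.0 |
| 112 vs 338 | 1.25 | 6.5 | 6.5 | 5.0 | 8.0 |
| 112 vs 338 | 1.5 | 7.9 | 7.9 | 5.0 | 11.1 |
| 112 vs 338 | 2 | 10.1 | 10.1 | 5.0 | 15.4 |
| 112 vs 338 | 0.67 | 2.8 | 3.0 | 4.8 | 1.6 |
| 112 vs 338 | 0.5 | 2.3 | 2.2 | 5.2 | 0.8 |
| 68 vs 382 | 1.5 | 9.1 | 8.9 | 5.0 | 14.1 |
| 68 vs 382 | 2 | 11.8 | 11.7 | 5.3 | 21.0 |
| 68 vs 382 | 0.5 | 1.1 | 1.1 | 5.1 | 0.2 |

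At N = 520 the results are nearly the same (25%: 7.9% at ratio 1.5, 9.7% at 2, 2.1% at 0.5). Across all scenarios Welch lies between 4.7% and 5.3%.

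A separate run at 115 vs 345 gave Mann–Whitney 6.2%, 7.3%, 10.9% and 2.1% at ratios 1.25, 1.5, 2 and 0.5. In that run Welch was at 4.9–5.3% and Brunner–Munzel at 4.6–5.2%.

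**Role of the imbalance.** With 240 vs 240, Mann–Whitney rejects 5.3% at ratio 1.5, 5.8% at 2 and 6.0% at 0.5. Most of the distortion therefore comes from unequal spread combined with unequal group size.

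**The case against.** **The tests carry little weight.** Section 3.5.4 makes a multivariable logistic regression the primary inference. Section 4.2 calls these comparisons descriptive in its heading, the Table 2 shell has no p-value column, and section 5.1 describes the study as exploratory. All of this stands and limits the importance of the point. It does not remove it, because section 3.5.2 still commits to formal testing.

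**The null hypothesis.** Mann–Whitney is valid for the null of identical distributions, and a variable with unequal spread is not under that null. This is formally true. But the heteroscedastic branch is used only once the spreads have been judged to differ, so that null has already been set aside. What remains of interest is location, and for location the level is not held.

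**The rule is better than the pooled t-test.** This also stands: at 112 vs 338 and ratio 1.5, 7.9% against 11.1%. The rule reduces the problem without curing it.

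**Readings that go too far.**

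- A reader might infer that every p-value from this rule is wrong. The documents do not support that. Mann–Whitney for non-normal variables is conventional and holds its level when the distributions are identical.
- A reader might quote much larger rejection rates for skewed data. With gamma data of equal means at 115 vs 345, Mann–Whitney rejects in 16% to 53%. These are not error rates, because the medians differ (0.918 and 0.839 against 0.959, all means 1), and nothing in section 3.5.2 makes the arithmetic mean the target for skewed variables. On the same data log-scale Welch rejects in 23% and 77%, and Brunner–Munzel in about 12% and 40%.
- A reader might add that a preliminary variance test inflates the error further. The article names no such test, and this effect was not quantified.

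**Conclusion.** Wrong as written, minor. For approximately normal measures with unequal variances, the stated rule picks a test that does not hold the two-sided 5% level at the expected group sizes. At about 1:3 the size is roughly 6%, 7–8% and 10–11% for SD ratios of 1.25, 1.5 and 2, and about 2% at 0.5. At about 1:5.7 it runs from about 1% (ratio 0.5) to about 12% (ratio 2). Welch stays near 5%.

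These figures rest on normal data, equal means and assumed SD ratios. Because the article gives no SDs, the size and even the direction of the error in this study are unknown. It would be wrong to infer that the study's main conclusions are at risk, because the logistic regression does not use this rule.

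**What to change.** In section 3.5.2, delete heteroscedasticity as a reason for Mann–Whitney and drop the equal-variance condition on the t-test. Suitable wording: approximately normal continuous measures will be compared by Welch's t-test, whether or not the variances are equal; Mann–Whitney is kept for markedly non-normal or ordinal measures. If a rank test is wanted where spreads differ, name Brunner–Munzel and state that its null is P(X<Y) = 0.5, not equal means.

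The cost is one line of text, with no further data and no change to the sample size. The abstract states that nobody has been enrolled and no data collected, so the change can be made now without any question of its being driven by results.

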#### Multivariable models

3.5.3

Logistic regression will assess the independent association between key vascular markers (e.g., dorsalis pedis RI, PI, waveform classification, baPWV, ABI/TBI) and PHQ-9 ≥ 10, adjusting for study center (as a fixed effect), age, sex, body mass index, smoking status, alcohol use, education level, marital status, hypertension, diabetes, dyslipidemia, relevant medication use, and histopathological severity (e.g., OLGA/OLGIM stage or Updated Sydney graded atrophy/intestinal metaplasia). Results will be reported as odds ratios (OR) with 95% confidence intervals (CI). We will restrict the number of predictors in the primary multivariable models to approximately 10–12, prioritizing predefined key vascular indices and major confounders, with additional variables explored only in sensitivity analyses.

In a secondary analysis, linear regression will evaluate the association between vascular indices and PHQ-9 as a continuous outcome. Prior to model fitting, collinearity among vascular indices (e.g., RI, PI, baPWV, ABI/TBI) will be assessed (e.g., via variance inflation factors); if substantial collinearity is detected, we will reduce the number of simultaneously entered vascular predictors or construct composite scores to improve model stability. Model assumptions will be checked; transformations or generalized linear models will be applied as needed. Continuous predictors will be modeled linearly in the primary analysis unless clear evidence of non-linearity is identified; if linearity assumptions appear violated, appropriate transformations or restricted spline terms will be explored in secondary analyses. The results of the prespecified logistic and linear regression analyses will be presented in Table 3.

**TABLE 3 T3:** Multivariable associations between vascular measures and depressive symptoms.

Table 3A | Logistic regression (outcome: PHQ-9 ≥ 10).			
Predictor	Model	OR (95% CI)	*P*-value
Dorsalis pedis RI (per 0.1 increase)	Model 1 (basic)		
Dorsalis pedis RI (per 0.1 increase)	Model 2 (extended)		
Dorsalis pedis PI (per 0.1 increase)	Model 1 (basic)		
Dorsalis pedis PI (per 0.1 increase)	Model 2 (extended)		
Monophasic vs. triphasic waveform	Model 2 (extended)		
baPWV (per 100 cm/s increase)	Model 2 (extended)		
ABI (per 0.1 increase)	Model 2 (extended)		
SDNN (per 10 ms increase)	Model 3 (with HRV)		
RMSSD (per 10 ms increase)	Model 3 (with HRV)		
Age (per 10-year increase)	All models (adjusted)		
Female sex	All models (adjusted)		
BMI (per 1 kg/m^2^ increase)	All models (adjusted)		
Hypertension	All models (adjusted)		
Diabetes mellitus	All models (adjusted)		
Dyslipidaemia	All models (adjusted)	–	–
OLGA stage III/IV vs. 0–II	All models (adjusted)	–	–
Model 1: adjusted for age, sex, body mass index (BMI), and conventional cardiovascular risk factors. Model 2: Model 1 plus histological severity of gastritis and standard arterial stiffness/peripheral artery indices (baPWV and ABI/TBI). Model 3: Model 2 plus heart rate variability (HRV) indices.			

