##### Dorsalis pedis artery ultrasound

3.3.2.1

Doppler angle correction (e.g., ≤60°) and sample volume placement are standardized across participants; at least three cardiac cycles are averaged for PSV/EDV-derived indices. Using B-mode imaging, the dorsalis pedis artery is visualized between extensor hallucis longus and extensor digitorum longus tendons. Measurements include arterial diameter and anatomic trajectory. Color and pulsed Doppler modes are then used to capture the full cardiac cycle waveform and derive:

① Peak systolic velocity (PSV)

② End-diastolic velocity (EDV)

③ Resistive index (RI = (PSV–EDV)/PSV)

④ Pulsatility index (PI = (PSV–EDV)/Vmean)

⑤ Flow waveform classification (triphasic, biphasic, or monophasic)

If feasible, vessel cross-sectional area and flow volume may also be estimated. By default, the right dorsalis pedis artery is assessed. If prior vascular surgery, deformities, or measurement constraints exist, the left side is used and documented. Bilateral measurements may be obtained in some cases to allow averaging or sensitivity analyses.

Consistency will be maximized by a harmonized acquisition protocol (probe type and frequency range, Doppler angle ≤ 60°, sample volume placement, wall filter/PRF, gain, sweep speed, and averaging over ≥ 3 cardiac cycles) with site-specific standardized presets and cross-site training. Where identical equipment is not feasible, the device model, transducer, and key presets will be recorded, and site/device effects will be explored in sensitivity analyses (and/or adjusted as covariates). Sonographers will be blinded to participants’ psychological scale scores and group assignments to minimize observer bias. Doppler images and waveform recordings will be centrally archived. A blinded secondary review of a randomly selected subset is performed by the lead center to assess cross-site consistency, and site/device effects will be examined analytically as sensitivity analyses. Waveform classification (triphasic, biphasic, or monophasic) will be analyzed as an ordinal categorical variable; in the blinded secondary review subset, any classification discrepancies will be resolved by adjudication at the lead center according to the prespecified waveform criteria.

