#### Incremental value analysis

3.5.4

Three hierarchical models for identifying PHQ-9 ≥ 10 at baseline will be compared:

① Model A (Clinical-GI Model): Demographics + cardiovascular risk factors + gastritis severity

② Model B (Vascular Multimodal Model): Model A + dorsalis pedis ultrasound + baPWV/ABI/TBI

③ Model C (Extended Multimodal Model): Model B + HRV metrics (e.g., SDNN, RMSSD)

Area under the ROC curve (AUC) and 95% CI will compare model performance. Among model-performance measures, AUC will be treated as the primary discrimination metric, whereas calibration indices, Brier score, and decision-curve analysis will be considered supplementary or secondary performance assessments. Model calibration will be assessed using calibration plots and, where appropriate, calibration slope/intercept and Brier score. We will additionally consider decision-curve analysis to evaluate potential clinical utility across plausible referral thresholds.

The primary inferential analysis will be a prespecified multivariable logistic regression model for PHQ-9 ≥ 10 including a limited set of predefined vascular exposures and major confounders. Linear models for PHQ-9 total score, penalized regression, composite-score approaches, and decision-curve analysis will be considered secondary or exploratory analyses. In the primary model, vascular predictors will be limited to a small prespecified set of clinically interpretable measures, such as dorsalis pedis RI and/or PI together with baPWV, while additional vascular or autonomic variables will be evaluated only in secondary or exploratory analyses.

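### The adjustment set in 3.5.3 (with centre as a fixed effect) is not the one in the Table 3 footnote, and incremental-value Models A–C omit centre, so a centre-aligned marker difference can pass as vascular signal.

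*Protocol article*

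**What the plan says.** **Text of 3.5.3.** The logistic model for PHQ-9 ≥ 10 is specified as "adjusting for study center (as a fixed effect), age, sex, body mass index, smoking status" and continues with alcohol use, education, marital status, hypertension, diabetes, dyslipidaemia, medication and histological severity. The same section states: "The results of the prespecified logistic and linear regression analyses will be presented in Table 3".

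**Table 3 footnote.** "Model 1: adjusted for age, sex, body mass index (BMI), and conventional cardiovascular risk factors". Then "Model 2: Model 1 plus histological severity of gastritis and standard arterial stiffness/peripheral artery indices (baPWV and ABI/TBI"). Model 3 adds HRV. Centre, alcohol, education, marital status and medication are not named, and neither Table 3A nor Table 3B has a centre row. The row "OLGA stage III/IV vs. 0–II" is assigned to all models in both parts of the table.

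**Section 3.5.4.** The baseline for the AUC comparison is "Model A (Clinical-GI Model): Demographics + cardiovascular risk factors + gastritis severity". Model B adds dorsalis pedis ultrasound and the stiffness and ankle/toe indices; Model C adds HRV. Nothing in the section brings centre in. (Table 3B reuses the letters A–C for its linear models; below, Models A–C means those of 3.5.4.)

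**Section 3.3.2.1.** Equipment may differ: "Where identical equipment is not feasible, the device model, transducer, and key presets will be recorded". Site and device effects go to sensitivity analyses, with covariate adjustment as an and/or alternative.

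**Section 3.3.** The general covariate list also omits centre.

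**The concern.** One regression has two adjustment sets, so the document does not fix which odds ratio will be reported. An analyst working from the table shell would leave out centre and four other covariates that the text requires, and the choice could be made after seeing the data.

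The gap is wider for Models A–C, because no text supplies centre. These models carry the incremental-information part of objective 3, and AUC is their primary discrimination metric. If centres with more screen-positive patients also record higher (or lower) marker values, through equipment, technique or case-mix, the marker stands in for centre. Model A cannot contain that information, so the gain is credited to Model B. Model C is exposed in the same way, because 3.3.3.2 allows HRV to be recorded supine or seated and on two kinds of device. The bootstrap in 3.7 corrects for overfitting; as described, it does not separate centre from marker.

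**Working it through.** **1. Where centre appears**

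| Specification | Centre named? |
|---|---|
| 3.3 general covariate list | no |
| 3.5.3 text, logistic model | yes, fixed effect |
| Table 3A, Models 1–3 | 0 of 3 |
| Table 3B, three linear models | 0 of 3 |
| 3.5.4, Models A–C | 0 of 3 |

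Histology enters at Model 2 by the footnote, but the OLGA row assigns it to every model, including Model 1. Both cannot hold.

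**2. The plan's sample size, reproduced**

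With 10 events per variable and a 25% event rate, N = 10 × predictors / 0.25. Ten predictors give 400 and twelve give 480, as stated in 3.6. Dividing by 0.90 gives 445 and 534, close to the stated 450–520.

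**3. What centre costs**

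Four centres as a fixed effect need 3 parameters. Added on top of 10–12, the model has 13–15. Expected events are 450 × 0.90 × 0.25 = 101 and 520 × 0.90 × 0.25 = 117. Events per variable become 101/13 = 7.8 and 117/15 = 7.8 (or 120/15 = 8.0 on the plan's own 120 events), below the stated 10. Keeping 10 would need 130/0.25 = 520 to 150/0.25 = 600 analysable participants, or 578 to 667 enrolled after dividing by 0.90.

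The covariates listed in the 3.5.3 text other than centre already number 12 at one parameter each. Centre (3) and two vascular markers bring that to 17, or 117/17 = 6.9 events per variable.

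**4. How large the bias could be**

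The documents give no centre-level prevalence and no device offset, so every value here is an assumption. Simulation: 468 participants (520 × 0.90), four equal centres, one normally distributed marker with no within-centre association, logistic regression, two-sided 5% level. The prevalences 15/20/30/35% average the plan's 25%. Aligned means that centres with higher prevalence also have higher marker means. Ranges cover several runs with 468–480 participants, 600–2,000 replicates and different spacing of prevalences and offsets; the ±0.3 SD row includes a run at ±0.25 SD.

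| Centre prevalence | Marker offsets | False positives, no centre | With centre | Spurious OR per SD |
|---|---|---|---|---|
| 15–35% | aligned, up to ±0.5 SD | 24–31% | about 5% | about 1.15 |
| 15–35% | aligned, up to ±0.3 SD | 10–14% | 4–5% | about 1.09 |
| 20–30% | aligned, up to ±0.5 SD | 9–11% | about 5% | about 1.07 |
| either | essentially uncorrelated with prevalence | 4–6% | about 5% | – |

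If prevalence or marker level is equal across centres, there is no inflation (about 5%). Averaging over all 24 orderings of the ±0.5 SD offsets gives about 12–13% at 15–35% prevalence and about 7% at 20–30%.

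**5. AUC gain in a very large sample (400,000), worst aligned case**

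| AUC of Model A | Gain, no centre | Gain, centre in both models |
|---|---|---|
| 0.61 | 0.007 | 0.000 |
| 0.70 | 0.0045 | 0.000 |
| 0.77 | 0.0035 | 0.000 |

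At 20–30% prevalence with ±0.5 SD the gain is 0.002 or less in the same range of Model A AUC. Over case/non-case pairs from the same centre, the spurious gain disappears (slightly negative, no lower than −0.007). These figures require a Model A with some discrimination: with none at all (AUC 0.50) the worst-case gain would be about 0.04.

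**The case against.** A reader might infer that the planned association analysis is not adjusted for centre. The document does not support that. The 3.5.3 text commits to centre explicitly, and Table 3 is an empty shell in a condensed article that can be read as an abbreviated display. For the primary association, harm arises only if the footnote is followed over the text. This objection stands: that part is a reconciliation error. It does not cover Models A–C, where no statement brings centre in.

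A reader might also infer that device differences will create vascular signal. The documents show only that they could. Presets are harmonised, recordings are archived and partly re-read blind, sonographers are trained to Kappa > 0.8, and devices are recorded. RI and PI are ratios of velocities, so a purely multiplicative velocity or angle error cancels. Wall-filter effects on end-diastolic velocity, baPWV devices, HRV conditions and case-mix remain. These safeguards make ±0.5 SD offsets less plausible, but they do not decide whether centre is in the model.

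Site intercepts do not carry over to new clinics, so including centre in a model meant for identifying patients is debatable. That is fair, and it favours the within-centre AUC. Nor do the documents require histology from Model 1 on; a staged build-up is legitimate if row and footnote agree.

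**Conclusion.** The point holds as a contradiction between 3.5.3, the Table 3 footnote and the Table 3 rows, and as a missing centre term in Models A–C. The false-positive figure of about 30% is an assumed worst case: prevalence of 15–35% across centres and offsets of ±0.5 SD in the same order. Milder aligned cases give 10–14%, and without alignment the rate stays near 5%. Centre in the model restores about 5% in every case tried. The AUC distortion is small, about 0.006 in the worst case for a Model A with an AUC of 0.6 to 0.7; the main exposure is the odds ratio and its p-value. All sizes rest on assumed centre differences, so the finding is that centre effects can pass as vascular signal, not that they will.

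**What to change.** 1. State centre as a fixed effect in Models 1–3 of Table 3A and in the Table 3B models, and make the footnote match the 3.5.3 adjustment set, including alcohol, education, marital status and medication.
2. Make the OLGA row and the footnote agree on the model at which histology enters. Either choice works.
3. For Models A, B and C, compute AUC and its increments over case/non-case pairs from the same centre, or include centre in all three alike.
4. Count centre's parameters (3 for four centres, more if sites are added) inside the 10–12 predictors and name the covariates that give way.

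The cost is wording and table shells; by the abstract, no participant has been enrolled. The real price is in item 4: 3 parameters for centre leave 7–9 for everything else, fewer than the full 3.5.3 list needs. If they are added on top instead, events per variable falls to about 8. The within-centre AUC costs no parameters.
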